## Assessments and Measures

### Psychometric assessments

#### Visual Analogue Scales (VAS)

Previously tested and sensitive VAS will be repeatedly used to better characterize subjective drugs effects over time [16, 44-46]. VAS will be presented as are 100 mm long horizontal lines marked with “not at all” on the left and “extremely” on the right [46]. The following VAS will be used: “drug effect”, “good effect”, “bad effect”, “liking”, “high”, “energy level”, “feelings of closeness to others”, “mind racing”, “ability to concentrate”, “fear”, “hungry”, “sedated”, “talkative”, “open”, and “confused”. Scales will be administered 4 h before and 0, 20, 60, 90, 120, 150, 180 min, and 4, 5, and 6 h after MDMA/placebo administration [45].

#### Adjective mood rating scale (AMRS)

An adjective mood rating scale (AMRS or EWL60S) is a 60-item Likert scale that allows repeated assessment of mood in 6 dimensions: activation, inactivation, well-being, anxiety/depressed mood, extro- and introversion, and emotional excitability. The scale is sensitive to the effects of MDMA [13, 24, 42, 47]. It will be used before, 75, 120 min and 5 h after MDMA administration. The German EWL60S version is used [48].

#### State-trait anxiety inventory (STAI)

The state-trait anxiety inventory (STAI) yields a score for state and trait anxiety levels [49]. The trait scale will be administered once. The state anxiety scale will be used before, 75, 120 min and 5 h after MDMA administration.

#### Addiction Research Center Inventory (ARCI)

The Addiction Research Center Inventory (ARCI) is a true-false questionnaire with five empirically derived scales: pentobarbital-chlorpromazine-alcohol group, a measure of sedation; morphine-benzedrine group, a measure of euphoria; lysergic acid diethylamine group (LSD), a measure of dysphoria and somatic symptoms; benzedrine group, a stimulant scale consisting mainly of items relating to intellectual efficiency and energy; and amphetamine, an empirically derived scale sensitive to the effects of d-amphetamine [50]. It has previously been shown to be sensitive to the effects of MDMA [16, 17] and is available in a validated German version [51]. The ARCI will be administered 4 h before and 150 min after MDMA administration.

#### Altered states of consciousness (5D-ASC)

The 5 dimensions of altered states of consciousness (5D-ASC) scale is a visual analogue scale consisting of 94 items [52]. The instrument is constructed of five scales and allows assessing mood, anxiety, derealization, depersonalization, changes in perception, auditory alterations, and reduced vigilance. The scale has repeatedly been used to evaluate subjective responses to MDMA [24, 42, 47] or other psychoactive substances [53]. The 5D-ASC scale will be administered once 4 h after MDMA administration to retrospectively assess drug peak effects.

### Physiological assessments

#### Vital signs

Blood pressure, heart rate, body temperature, and pupil diameter will be recorded at -4 h, 0, 20, 40, 60, 90, 120, 150, 180 min, and 4, 5, and 6 h after MDMA/placebo administration. Blood pressure (systolic and diastolic) and heart rate will be measured on the leading arm using an automatic oscillometric device. Heart rate will also be measured continuously with a RS 800 Polar device (Polar Electro Oy, Kempele, FIN), set to sample the average heart rate every 5 s, and analyzed using Polar Precision Performance software. Body temperature will be measured using an ear thermometer. Ambient temperature is also recorded trice on the experimental day. Pupil diameter and the reaction to a light stimulus will be recorded using a handheld dynamic pupillometer (PRL-200, Neuroptics, Irvine, CA, USA).

#### List of complaints (LC) and Adverse effects (AE)

Adverse effects (AE) will be assessed systematically during the session using a modified list of complaints (LC) [54]. The scale consists of 66 items, yielding a global score measuring physical and general discomfort. The LC list is administered 4 h before and 180 min after MDMA/placebo. An additional LC is completed 24 h after MDMA/placebo in the absence of the experimenter. Additional AE during the session will be listed in the case report form (CRF) 5 h after MDMA/placebo administration. Subjects will also be asked to report AE between study sessions at the beginning of the next session.

### Cognitive and psychomotor function

#### Reading the mind in the eyes test (RME)

A 10-min computerized “Reading the Mind in the Eyes Test” is performed 90 min after MDMA/placebo administration (before the CRTT). The test assesses drug effects on inferring mental states from the eye region. 36 pictures of the eye regions of different persons will be presented to the participants on a computer screen with four alternative labels describing what the person displayed might be thinking or feeling at the moment [55].

#### Choice reaction time test (CRTT)

This five choice reaction time test (CRTT) assesses a combination of sustained attention and executive motor function [56]. The CRTT will last for 3 min and requires the subject to quickly and accurately press a button of the same color as the one of five (red, blue, white, yellow, or green) which flashed. The stimuli are presented in random sequence. Using a computer-based algorithm, the interstimulus interval is adjusted by 50 ms according to performance in a continuously moving window of the last seven stimulus–response pairs. The interstimulus interval decreases when four or more stimulus–response pairs were correct; otherwise, the interval increases. Thus, test difficulty is adjusted to achieve a subject false response rate of 50%, which makes for a demanding task. The dependent variable is the mean reaction time (for correct responses) for the last 2 min of the test. Reaction times less than 300 ms will be considered artifactual and are therefore discarded. Subjects will go through one training session at the beginning of each session. Tests will then be performed 0 min and 90 min after MDMA administration.

#### End of Session Questionnarie

At the end of each session, participants will be asked to indicate how much they liked the drug overall and how strong the overall effect was on separate VAS [16].

### Neuroendocrine function

MDMA increases cortisol, prolactin, catecholamine, and 5-HT concentrations in plasma in humans [43, 57-59]. MDMA also increases vasopressin (AVP) potentially leading to hyponatriemia [59, 60]. We will test the effect of duloxetine on MDMA-induced increases in plasma cortisol, prolactin, catecholamines, serotonin, and metanephrines (norepinephrine and epniephrine metabolites). Plasma cortisol and prolactin samples will be collected at 0 min and at 120 min (tmax) after MDMA/placebo administration (2x7.5 ml blood). Copeptin is the C-terminal part of provasopressin. Copeptin is released stoichiometrically together with AVP and is easier to measure than AVP. Copeptin samples will be collected at 0 min and 120 min after MDMA/placebo administration when peak AVP values are expected [59] (2x7.5 ml blood). Plasma and urine sodium, urea, and osmolality are simultaneously assessed (2x7.5 ml blood, 2x10 ml urine). Catecholamine and metanephrine samples will be collected at 0, 60, and 120 min after MDMA/placebo administration (3x7.5 ml blood).

### Blood sample collection (pharmacokinetics)

Blood samples (11x7.5 ml) will be collected on the study day -4, 0, 0.33, 0.67, 1, 1.5, 2, 2.5, 3, 4, and 6 h after MDMA or placebo administration. This will allow us to assess the pharmacokinetics of both MDMA and duloxetine and potential PK interactions of the two compounds. The design is optimized to assess effects of duloxetine on peak plasma levels of MDMA (time to Cmax = 2h) and AUC0-6h for MDMA [43]. Blood samples will be collected in heparinized tubes, centrifuged at 4C at 2000 rpm for 10 min, and the plasma is then stored at -20C (two aliquots) until analysis. Collection tubes labels will include the following information: study number, study day, subject number, and sample number. The date and actual blood sampling time will be recorded on the sample collection page in the CRF.

#### Amount of blood samples

On each study day a total of 20 blood samples (20x7.5 ml = 150 ml) will be collected on the study day. During the whole study approximately 600 ml of blood are collected. This amount to 20% more than a standard blood donation. However, blood is collected in amounts of 150 ml every 2 weeks spread out over 6 weeks and not at once which allows for regeneration. In order to blind the study, plasma samples will be collected also on the placebo day.

### End of Study (EOS) visit

#### EOS Examination

Clinical examination and vital signs. Blood tests: Na, K, creatinine, ASAT, ALAT, -GT, hemoglobin, hematocrit, white blood cell count, red blood cell count, platelet cell count. Adverse effects.

#### EOS Questionnaire

A debriefing interview will be performed including a retrospective comparative evaluation of the subjective experience of all four study sessions. Subjects will be asked to rate the overall drug effect for each of the four sessions. Subjects will also be asked to guess the assignment of the study drugs to the four study sessions to assess whether subjects were able to distinguish the study conditions (duloxetine vs. placebo). They will also be asked to provide a feed-back on the study and their experience and to indicate whether they would take the drug again in a controlled or recreational setting [15].

## Study Drugs

### Duloxetine

Duloxetine (Cymbalta) is a potent and selective 5-HT and NE reuptake inhibitor [27]. Duloxetine (60 mg gelatine capsules) will be obtained from Eli Lilly (Suisse) SA, Vernier. The investigator pays for the product. Eli Lilly does not act as a sponsor for the study. The original company product will be used. However, capsules will be encapsuled with opaque dark-colored gelatine capsules and similar placebo capsules containing lactose will be prepared by a pharmacist. **Clinically used doses:** Duloxetine is used clinically in the treatment of depression, generalized anxiety disorder, diabetic and other neuropathy, and fibromyalgia. The clinically used common starting dose is 60 mg/day. Maintenance doses are 60-120 mg/day [25, 61, 62]. Several clinical trials have used 120 mg/day given once or in two doses of 60 mg twice per day. The suggested maximum dose is 120 mg daily. **Tolerability:** Duloxetine was well tolerated at doses of 60-120 mg/day [63]. See 14.1. for expected adverse effects of duloxetine. **Pharmakokinetics (dose finding and dosing intervals):** Elimination half-life of duloxetine is 12 h and Tmax is 6 h [61, 64]. On the test day, duloxetine (120 mg) will be given at 8 AM 4 h before MDMA administration at 12 AM so that the duloxetine Cmax will be reached shortly after the onset of the subjective MDMA effect (1h after MDMA administration) and together with Cmax of MDMA. An additional dose of duloxetine (120 mg) will be administered the day before MDMA at 8 PM, 16 h before MDMA administration. At both time-points duloxetine will be administered in a dose of 120 mg (maximum suggested therapeutic dose). Because the study uses only one dose of duloxetine it is important to use a relatively high dose to ensure effective plasma levels. Mean duloxetine plasma Cmax values were 22, 44, and 61 ng/mL after single oral doses of 30, 60, and 90 mg of duloxetine in healthy volunteers [64]. At steady state 40 mg once daily resulted in a mean Cmax level of 35 ng/mL and a trough level of approximately 10 ng/mL at 24h [32]. Population PK studies showed mean Cmax levels of 30-60 ng/mL follwing daily administration of 60 mg and depending on gender, smoking status, age and other variables [65]. Mean trough levels at 24h were in the range of 25 ng/mL. Women typically had 64% higher average steady-state concentrations than men (with considerable overlap). Similarly, nonsmokers had 43% higher average concentrations than smokers. Doubling the duloxetine dose from 30 mg to 60 mg and from 60 mg to 120 mg resulted in 2.3 fold and 2.6 fold higher average concentration values, respectively [65]. Based on these data we expect mean Cmax levels of 120-150 6 h after the administration of the second dose of 120 mg of duloxetine with the first dose (120 mg) given 12 h before the second dose. This Cmax is similar to the one seen in patients treated with daily doses of 120 mg under steady state conditions (peak 100 ng/mL, trough 50 ng/mL) [65]. **PD and PK interactions of duloxetine and MDMA** (see 7.2.1/2). **Relevant clinical studies using duloxetine in healthy volunteers**: Duloxetine (60 mg for 14 days) was not able to block the thyramine-induced increases in systolic blood pressure, indicating that the dose might be too low to block the NE transporter to a relevant extent in this test [66]. A dose of 80-120 mg was effective in suppressing the blood pressure increase due to thyramine [25]. However, there is clinical evidence that lower doses of duloxetine block NE transport. For example, urine catecholamine changes indicative of NE reuptake inhibition were present already at 80 mg. We suggest that a dose of 120 mg should be used for the present study. Of note, desipramine completely blocked thyramine-induced SBP responses which could indicate that desipramine interacts with stimulants at a different site on the NE transporter than duloxetine.

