## Schedule of experimental session

**Table 2** shows the schedule of events for each experimental session. Each of the four test sessions will last 10 h from 8:00 AM to 6:00 PM. Subjects will arrive at 8:00 AM at our CRC. Subjects will take duloxetine (120 mg) or placebo the night before the study session at 8:00 PM and another dose of duloxetine (120 mg) or placebo in the morning of the study day (8:00 AM). An indwelling intravenous catheter will be inserted into a subcutaneous vein of the forearm of the nondominant arm. MDMA (125 mg) or placebo is administered 4 h after duloxetine (12:00 AM). The acute effects of MDMA are expected to last for 4 h [42, 43]. Outcome measures (see below) will repeatedly be assessed during the study session. The sessions end at 6 PM. Subjects will be under continuous medical control until the effects of the drug have completely subsided (within 4-6 h after MDMA administration).

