## Potential risks

Physical risks:

MDMA: A large series of phase I like studies have been performed using MDMA [13-16, 24, 42, 44-47, 57, 58, 67, 68, 70, 71, 74, 75, 82-91]. This considerable body of evidence indicates that the likelihood for significant toxicity from doses of MDMA such as the one to be used in the present study and in controlled settings is very low. Thus, no lasting biological or psychological injury is expected. See below for specific MDMA toxicity and monitoring. Expected adverse effects of MDMA:MDMA is expected to produce moderate acute adverse effects such as increased jaw muscle tension, dry mouth, dizziness, palpitations, tremor, nausea, headache, insomnia, and transient anxiety in more than 10% of subjects, [15, 42]. MDMA is expected to produce sequelae (1-3 days post MDMA) including difficulty concentrating, irritability, or slightly depressed mood in more than 10% of subjects [15]. No severe or serious adverse effects are expected. Duloxetine: In placebo-controlled double-blind trials in patients duloxetine (60-120 mg/day) produced nausea (20-29%), headache (20%), dry mouth (15-18%), insomnia (11-15%), fatigue (14%), dizziness (9-11%), constipation (11%), decreased appetite (8%), and sweating (6%) [63]. Adverse effects of duloxetine in healthy volunteers similary include nausea, dry mouth, insomnia, dizziness, sweating, and clinically non-significant increases in blood pressure or heart rate [25, 61, 92]. No severe or serious adverse effects are expected.

Venipunction: There is a risk for pain, bruising and thrombophlebitis.

Risk to privacy of subjects: Potential risks of data collection include breach of confidentiality. Financial risks: There is no risk of expense to the subject. Insurance coverage is provided. Travel expenses are expected to be minimal and are included in the compensation of 1000 CHF per subject.

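### Section 11.5.1 plans 240 mg of duloxetine within 12 h against its own stated maximum of 120 mg daily, and calls a predicted peak similar to one that it exceeds by 20-50%

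*Protocol*

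**What the plan says.** On the ceiling, section 11.5.1 states: "The suggested maximum dose is 120 mg daily". It also describes 120 mg/day in clinical trials as either one dose or two doses of 60 mg.

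On the regimen, the same section says: "An additional dose of duloxetine (120 mg) will be administered the day before MDMA at 8 PM, 16 h before MDMA administration". Section 11.3 adds, after the evening dose, "another dose of duloxetine (120 mg) or placebo in the morning of the study day (8:00 AM". The Summary gives the same two doses, 16 h and 4 h before MDMA. Section 11.5.1 then labels them: "At both time-points duloxetine will be administered in a dose of 120 mg (maximum suggested therapeutic dose".

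On exposure, section 11.5.1 expects a mean Cmax of 120-150, without a unit, 6 h after the second dose. It continues: "This Cmax is similar to the one seen in patients treated with daily doses of 120 mg under steady state conditions (peak 100 ng/mL", with a trough of 50 ng/mL.

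On risk, section 14.1 reports: "In placebo-controlled double-blind trials in patients duloxetine (60-120 mg/day) produced nausea (20-29" per cent, followed by other rates from the same dose range. The tolerability sentence in 11.5.1 also refers to 60-120 mg/day. The healthy-volunteer effects listed in 14.1 carry no dose. Section 14.1 concludes that nothing severe or serious is expected from duloxetine.

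**The concern.** A daily ceiling has turned into a per-dose ceiling without comment. A reader of section 11.5.1 is told that the study works at the maximum suggested dose and reaches a familiar peak level. The section's own figures show twice the stated daily amount inside 12 h, and a predicted peak wholly above the level it is compared with.

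The ethics committee and the investigators judge the regimen from this text, and the subject information on risk draws on the same ground. The predicted duloxetine peak is deliberately timed to coincide with the MDMA peak. Section 14.4.3 takes excessive monoamine release seriously enough to set triggers for early analysis and possible termination. The description of duloxetine exposure, and the doses behind the quoted adverse-effect rates, should therefore agree with the regimen actually planned.

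**Working it through.** **Inputs, all from the protocol**
- Stated maximum: 120 mg daily (11.5.1).
- Doses: 120 mg at 8 PM and 120 mg at 8 AM, 12 h apart (11.3, 11.5.1).
- Kinetics: "Elimination half-life of duloxetine is 12 h and Tmax is 6 h" (11.5.1).
- Single-dose data: "Mean duloxetine plasma Cmax values were 22, 44, and 61 ng/mL after single oral doses of 30, 60, and 90 mg" (11.5.1).
- Predicted mean Cmax: 120-150, taken as ng/mL (11.5.1).
- Comparator: steady-state peak of 100 ng/mL on 120 mg daily (11.5.1).
- Doses behind the tolerability statement and the adverse-effect rates: 60-120 mg/day (11.5.1, 14.1).
- Hypothesised rise of duloxetine Cmax caused by MDMA: below 30% (9.2).

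**1. Reproducing the predicted Cmax**

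Dose-proportional scaling to a single 120 mg dose gives:
- 22 × 120/30 = 88 ng/mL
- 44 × 120/60 = 88 ng/mL
- 61 × 120/90 = 81.3 ng/mL

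The second peak comes about 12 h after the first, which is one half-life. If half of the first peak remains, the two-dose factor is 1 + 0.5 = 1.5:
- 88 × 1.5 = 132 ng/mL
- 81.3 × 1.5 = 122 ng/mL

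A one-compartment oral model uses ke = ln 2/12 per h, with ka solved from ln(ka/ke)/(ka − ke) = 6 h. This gives ka = 0.365 per h and a two-dose peak factor of 1.615:
- 88 × 1.615 = 142 ng/mL
- 81.3 × 1.615 = 131 ng/mL

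Both methods together give about 122-142 ng/mL, inside the stated 120-150. The number reproduces.

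**2. Dose against the stated maximum**
- 120 + 120 = 240 mg within 12 h.
- 240/120 = 2.0 times the stated daily amount in a 24-h window.
- Against the protocol's own description of split dosing, each planned dose is 120/60 = 2 times as large.

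**3. Predicted peak against its comparator**
- 120/100 = 1.2 and 150/100 = 1.5, so the predicted range is 20-50% above the comparator.
- In the other direction, 1 − 100/120 = 17% and 1 − 100/150 = 33%, so the comparator is 17-33% below the predicted range.
- If MDMA raised duloxetine Cmax by the full 30% that bounds the hypothesis in 9.2: 120 × 1.3 = 156 and 150 × 1.3 = 195 ng/mL. This is an upper bound, not an expectation. It shows only that the printed multiple is stated before any MDMA effect.

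**4. How far apart two doses and steady state should be on half-life alone**
- With simple halving, the once-daily steady-state factor is 1/(1 − 0.25) = 1.333, and 1.5/1.333 = 1.125.
- In the one-compartment model the steady-state factor is 1.407, and 1.615/1.407 = 1.148.
- Pure superposition therefore puts the two-dose peak 13-15% above the once-daily steady-state peak, less than the 20-50% between the protocol's printed figures.

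**5. Coverage of the risk text**
- 120/240 = 0.5 and 60/240 = 0.25. The quoted rates come from daily amounts of a quarter to a half of what is planned within 12 h.
- The protocol gives no adverse-effect rate at a stated dose above 120 mg/day, so no size can be put on any difference in risk.

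**The case against.** The strongest defence has four parts.

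*Calendar days.* Each date carries only 120 mg, both doses are stated openly, and the protocol never claims to stay within 120 mg per 24 h. The openness stands. The calendar reading does not rescue the text: section 11.5.1 treats 120 mg/day as a single dose or two of 60 mg, and this plan gives 120 mg at each of two times 12 h apart.

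*Disclosure.* The predicted range and the comparator stand in adjacent sentences, so nothing is hidden. That is true, and it limits the point to the description. The description still disagrees with the figures beside it.

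*Looseness.* The section reports mean peaks of 30-60 ng/mL at 60 mg daily, averages 64% higher in women and 43% higher in nonsmokers. Superposition alone gives an excess of only 13-15%. So the word similar is loose and not grossly wrong. The protocol printed 120-150 against 100, however, and a stated multiple would serve the reader better than an adjective.

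*Safety provisions elsewhere.* The Cmax passage sits under dose finding and dosing intervals, and aims at effective levels. Monitoring is in 14.2.6, and the interim analysis and triggers are in 14.4.3. It would be too strong to call the Cmax comparison the protocol's safety argument. Those provisions do not correct the dose label or extend the range of doses behind the rates in 14.1.

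A reader might also infer that the predicted Cmax itself is too low, because 11.5.1 quotes a 2.6-fold rise in average concentration from 60 to 120 mg: 44 × 2.6 × 1.5 = 172 ng/mL. The document does not support that step. The factor concerns average concentrations from another source than the single-dose peaks. For 30 to 60 mg that source gives 2.3-fold, while the single-dose peak rose 44/22 = 2.0-fold. From 60 to 90 mg the peak rose 61/44 = 1.39-fold for 1.5 times the dose. The single-dose peaks are about dose-proportional or less.

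**Conclusion.** The point holds as an internal contradiction in the dose and exposure text, with a gap in the risk text.

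- The regimen is 2.0 times the stated daily maximum within one 24-h window, is labelled as the maximum, and the excess is not acknowledged.
- The predicted mean Cmax is 1.2-1.5 times the peak it is called similar to, before any increase from MDMA.
- The tolerability statement and the quoted adverse-effect rates come from at most 120 mg/day and do not cover the planned regimen.

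This rests on reading the stated maximum as a limit per 24 h, and on taking the missing unit as ng/mL. It does not show that the 120-150 prediction is wrong; that range reproduces under dose-proportional scaling. Nor does it show that risk is understated by any given amount, because the protocol has no rates at a stated dose above 120 mg/day. It gives no basis for saying which dose is right.

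**What to change.** 1. In 11.5.1, reconcile the stated daily maximum, the two-dose regimen and the label attached to each dose, and carry the result into 11.3 and the Summary. Which dose is right is for the clinical investigators.
2. In 11.5.1, print the unit of the predicted Cmax. Replace the claim of similarity with the protocol's own multiple: 1.2-1.5 times the steady-state peak on 120 mg daily, before any increase from MDMA.
3. In 14.1 and in the tolerability sentence of 11.5.1, state that the figures come from at most 120 mg/day, half or less of the amount planned within 12 h, and that the document gives no rates for the planned regimen.

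The cost is protocol wording. The stated exposure comparison becomes slightly less favourable.
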